#### Informed Consent for People With MCI

Participants provided written informed consent, even though the acquisition of informed consent from people with MCI is a long-debated issue. Although degenerative neurological syndromes over time lead to a progressive decline in cognitive functions and the ability to express valid consent, the diagnosis of Alzheimer’s disease or MCI does not, in itself, lead to the loss of this ability. The legal capacity and the capacity to act remain, unless proven otherwise, from the age of adulthood until the death of the person. In fact, only a judicial measure can protect an individual with MCI who is unable to provide informed consent by appointing a legal representative. From a neuropsychological point of view, the impairment of executive functions (abstraction ability, problem solving, judgment and criticism, planning, planning, farsightedness, decision-making) is directly proportional to the decrease in capacity both in a general sense and in specific fields: health and economic decisions, driving skills, etc. However, these cognitive functions can be spared in the early stages of the disorder (MoCA score=21-24), unlike other functions that are affected early, such as memory and orientation. It is also common clinical experience that even if unable to understand the contents of a standard informed consent form (which must certainly be simplified), an individual with MCI is often able to express their choices in line with their lifestyle, preferences, and values. This underlines the importance of preserving the possibility for potential participants to use their skills to share possible choices.

Informed consent is a legal condition in which an individual accepts an action that is proposed to them (in our case, active participation in the feasibility study). To be informed, consent must be based on a full understanding of the action itself and the implications it can have. This implies the following:

Every effort must be made to guarantee and respect any residual capacity for autonomous decisions, considering consent as an instrument through which the subject realizes their autonomy.The autonomy of the subject requires that all information be understood.The person’s consent presupposes their ability to choose freely based on their preferences, moral values, life stages, and circumstances.

First, it was necessary to inform the older adults with MCI by adapting the information to their cognitive abilities, making every effort so that they could directly or indirectly communicate their preferences. The opinion of family members, for example, could be requested but was considered secondary to that of the patients. Older adults with MCI who gave their informed consent to participate but were not comfortable during the sessions had the option to withdraw from the trial at any time without any consequences.

In the specific case of the engAGE PoC, neither were serious, harmful effects on the patients with MCI foreseeable nor was there bad faith in the treatment proposal. The research teams proceeded to ask the older adults with MCI to provide their informed consent to participate and strive to do the following:

Ensure that they clearly understood the content of the information sheet and the consequences of their participation.Create the best conditions in which they can ask questions and express their will.Monitor throughout the course of the trial the persistence of their willingness to participate.

During the clinical interview, the contextual assessment of the ability to express an autonomous choice was carried out, assessing the presence of the following:

Ability to express a choiceAbility to understand information relating to consentAbility to give due weight to the situation and its possible consequencesAbility to use information rationally

If this evaluation gave a positive result, informed consent was acquired from the individual. Time and effort were devoted to providing correct and full information, the information sheets and the consent form were read together with the individual with MCI and their caregiver, an opportunity to ask questions was provided, and the best conditions were created to decide. An additional opinion was requested from the main and reference caregivers on whether the individual with MCI should participate in the project and what wishes and feelings about participation might not have been expressed. If the subject showed signs of dissent before and during each training session or showed behaviors that suggested that they were no longer willing to participate, the sessions were terminated, and the consent was automatically withdrawn.

#### Safety and Security Considerations

The hardware devices used are commercial devices and Conformité Européenne (CE) certified. The engAGE platform dashboards for older adults and caregivers are loaded on a tablet held by the users.

Personal data collected during the trial were, and are still being, handled and stored in accordance with the General Data Protection Regulation (GDPR) [40]. All data and documentation related to the trial are stored in accordance with applicable regulatory requirements, and access to data is restricted to authorized trial personnel. The project is committed to the maintenance of participants’ anonymity and confidentiality throughout all procedures, including screening, recruitment, testing, evaluation, and dissemination procedures. Data collection, usage, and storage procedures complied with national laws and the GDPR [40], including the commitment to participants’ right to access information, right to be informed, right to withdraw, and right to data erasure. Moreover, the servers are in the European Union and compliant with the GDPR. Use of the study data is controlled by the principal investigator. Data collection is compliant with the principle of data minimization, that is, the collection of personal information from study participants is limited to what is directly relevant and necessary to accomplish the specific goals of the testing and evaluation work packages. Data entry was carried out using specific software, providing blocks and data entry checks to reduce the number of entry errors. All screening data were discarded upon project completion. During the testing procedures, all visual, auditory, and sensory data that the robot collected and processed to function as planned were discarded after the procedures were completed. The exception to this is the collection of the number of interactions that the robot logged with each participant. However, these interactions were anonymous. All research data will be made openly available for secondary analysis 3 years after project completion. The study findings will be used for publication in peer-reviewed scientific journals and presentations in scientific meetings. Summaries of the results will also be made available to investigators for dissemination within their clinics.

In the case of the engAGE project, a critical area of security is the servers (in the cloud or on the premises) on which the solutions are deployed or data are stored. These have been provided with physical and logical protection. In addition, the communication network architecture implements mechanisms of comprehensive network protection against intrusion, such as an intrusion prevention system, a firewall, and a network antivirus filter. The core system is placed in a secure zone, excluding the necessary communication modules located in the demilitarized zone, enabling data exchange with engAGE services, devices, and components. In the case of communication via an external network, strong mechanisms are required to guarantee the protection of transmitted data, as well as their integrity, confidentiality, and nonrepudiation (eg, Transport Layer Security [TLS]). Authorization procedures have been implemented, specifying who is authorized to access the network and network services (access to services should be possible only for authorized users/devices by providing authentication and authorization mechanisms). Access to individual apps must require a user identifier and authentication (password, authentication certificate). The app functionality available to individual users is limited by each user’s rights. The system architecture includes solutions that eliminate or significantly reduce the system’s vulnerability to attacks, as recommended in the Open Web Application Security Project (OWASP). Data are transferred using REST (Representational State Transfer) application programming interfaces (APIs) using HTTPS. In engAGE, different types of databases are used for storing data. These database servers give the option of encryption at several levels and provide flexibility in protecting data from disclosure (eg, password storage encryption, data partition encryption).

## Results

Recruitment started in October 2023 and continued until April 2024, when there was still time to attend 80% of the trial in the three sites. At the end of recruitment, 40 (81.6%) of the total 49 older adults with MCI were assigned to the EG and 9 (18.4%) to the CG. The PoC started in November 2023 and ended in July 2024. The start and end dates were different across countries because of the various difficulties encountered in organizing the trial and recruiting end users in each site. The efficacy of the engAGE platform will be demonstrated on the basis of the improvement or maintenance of cognitive capacity. In addition, the effects on the quality of life and social connectedness of primary end users, as well as the reduction in the care load and stress of caregivers, will contribute to determining the importance of the platform. Furthermore, the feasibility of the engAGE intervention will be assessed on the basis of the usability and acceptance of the platform, both measured through standardized quantitative scales. Data analysis was completed at the end of 2024, and the results will be published at least by 2026.

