**Results:**

Data collection commenced in November 2023 and finished in July 2024, with the enrollment of 49 older adults with MCI (n=40, 81.6%, assigned to the experimental group [EG] and n=9, 18.4%, to the control group [CG]) conducted from October 2023 to April 2024. Data analysis was concluded in November 2024, and results will be published by 2026.

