### The RCT Phases

The PoC procedure was divided into three different phases after recruitment of the participants: baseline evaluation (T0), midterm evaluation (T1; after 3 months from T0), and final evaluation (T2; after 6 months from T0); the aim was to collect data, as described in Textbox 1. All questionnaires and scales at each phase of the PoC were administered through face-to-face interviews by eligible professionals at health care facilities.

Proof-of-concept (PoC) phases.

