### Data Analysis

This subsection describes the measurements, statistical tests, and tools with which the data collected in the engAGE PoC were, and are still being, analyzed. The different types of data that were collected in the engAGE project are as follows:

Credentials: username, password, email address, and similar security information used for authentication and account access in different services of the platformPersonal data: first name, last name, gender, age, weight, height, email address, contact address, and phone number of older adults in different services of the platformAnswers to specific questions in self-assessment questionnaires on MEMASGames score from Pepper appsMeasurements and monitored parameters: weight, heart rate, blood pressure, and physical activities gathered through the monitoring infrastructureHistorical data of the measurements and monitored parameters for training and using ML algorithms for each older adult in the ML service

In the engAGE testing and evaluation phase, the following data were, and are being, processed:

Information and results from questionnairesCognitive game scoresHistorical data of measurements collected for each end userAny information the end users decided to share through discussions/interviews, as well as data providing feedback from trialsOutcomes that concern feasibility (ie, the primary interest of the engAGE PoC): recruitment rate (proportion of eligible individuals who consent to participate in the study, ie, those who attended more than 80% of weekly sessions), retention rate (proportion of participants who completed the 6-month intervention period), and adherence to the intervention (average number of interactions with the Pepper robot during weekly sessions, the frequency of use of the MEMAS app, and the activity tracker recording time)

Descriptive statistics (means, SDs, medians, IQRs) will be used to summarize adherence metrics.

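### Recruitment until April 2024 with a July 2024 end leaves at most about two thirds of the 6-month course, not the stated 80%, and no room for a 6-month T2

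*Protocol article*

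**What the plan says.** **Dates.** The Results section states that recruitment began in October 2023 and "continued until April 2024, when there was still time to attend 80% of the trial in the three sites". It continues: "The PoC started in November 2023 and ended in July 2024". The abstract gives the same two windows: "Data collection commenced in November 2023 and finished in July 2024", with enrolment "conducted from October 2023 to April 2024". Results adds a qualification about sites: "The start and end dates were different across countries because of the various difficulties encountered in organizing the trial".

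**Design.** The section on the experimental group (EG) plans one robot session of about an hour each week for 6 months. The RCT Phases section places a midterm evaluation (T1) 3 months after T0, and the "final evaluation (T2; after 6 months from T0".

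**Rules that depend on the length of follow-up.** The Data Analysis section lists feasibility outcomes, which it calls the primary interest. One of them is the "retention rate (proportion of participants who completed the 6-month intervention period". Within its recruitment-rate wording it also refers to attendance at more than 80% of the weekly sessions, and it restricts the analysis to participants with adherence of at least 80%. It does not say what the 80% is a percentage of.

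**The concern.** The 80% in the Results sentence is the same figure as the adherence threshold for entering the analysis. It therefore reads as an assurance that everyone recruited, up to the last, could still qualify. If the calendar does not allow that, three things follow for late entrants.

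- **Retention.** Someone who starts too late to complete 6 months before the trial closes counts as not retained, however willing they were. A feasibility measure then partly reflects when recruitment happened.
- **Adherence and the analysis set.** For the EG there are two alternatives. If adherence is counted against the planned course, late entrants are excluded for administrative reasons. If it is counted against the sessions available to each person, they are admitted with a shorter exposure.
- **T2.** Any final evaluation held before the July close is early for these participants, in either arm. Change scores labelled as 6-month changes would then mix different intervals. If entry times differ by arm, the interval is confounded with arm, and the control group (CG) has only 9 people.

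**Working it through.** **Inputs**
- Last recruitment month: April 2024 (abstract; Results).
- End of trial and of data collection: July 2024 (abstract; Results). I take 31 July, the most favourable day.
- Planned course: weekly for 6 months (The Experimental Group). Six months = 365.25 / 2 = 182.6 days, or about 26 weekly sessions. The article does not state the 26; it is derived.
- T2: 6 months after T0 (The RCT Phases).
- Entry is taken as T0 and first session on the same day. Any delay between recruitment and start makes the result worse.

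**Formulas**
- Days available = 31 July 2024 minus entry date.
- Share of course = days available / 182.6.
- Maximum sessions = whole weeks available + 1, compared with 26.

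**Attempt to reproduce the stated 80%**

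| Entry | Days to 31 July | Share of 6 months | Maximum sessions | Share of 26 |
|---|---|---|---|---|
| 1 April | 121 | 121/182.6 = 66% | 17 + 1 = 18 | 69% |
| 15 April | 107 | 107/182.6 = 59% | 15 + 1 = 16 | 62% |
| 30 April | 92 | 92/182.6 = 50% | 13 + 1 = 14 | 54% |

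The stated 80% is not reproduced for any April entry.

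**Latest start dates that would work**
- 80% of the time: 0.8 × 182.6 = 146 days; 31 July minus 146 days = 7 March 2024.
- 80% of the sessions: 0.8 × 26 = 20.8, so 21 sessions, spanning 20 × 7 = 140 days; 31 July minus 140 days = 13 March 2024.
- T2 at 6 months: start by 31 January 2024. Conversely, an April entrant's 6-month T2 would fall in October 2024, after the stated end.

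**Other readings**
- Recruitment closing on 31 March: 122 days, 122/182.6 = 67%.
- Trial ending on 1 July: 91 days (50%) from 1 April, 62 days (34%) from 30 April.
- 24 planned sessions instead of 26: 18/24 = 75% for a 1 April start.
- "The trial" read as the whole November to July window of 274 days, counting both end days: 122/274 = 45% from 1 April.
- A site with its own shorter window: 122 remaining days are 80% of 122/0.8 = 152.5 days, or 5.0 months. The sentence is true at a site only if its whole programme lasted about 5 months or less, which contradicts the 6-month course and the 6-month T2.

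No reading consistent with a 6-month course reaches 80%.

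**The case against.** The strongest defence is that dates differed by country. It does not help. July 2024 is the overall end, so no site runs past it, and a site that closed earlier gives an April entrant less time.

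Four further objections limit the point, and they stand.

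1. **The number affected is unknown.** Recruitment until April is compatible with a single late entrant. The article does not say how many of the 49 entered after January or mid-March, in which arm, or how their T2 was handled. February to April are 3 of the 7 recruitment months, but that counts months and not people.
2. **The two effects of the adherence rule are alternatives.** A reader might infer that the filter removes late EG entrants and that the analysis also pools exposures as short as 3 months. Both cannot hold for the same EG participants. Counted against about 26 sessions, the analysed EG would have started by about 13 March and have roughly 4.6 (140/30.4) to 6 months. Counted against available sessions, nobody is dropped by calendar and only the mixed exposure remains.
3. **The link from sessions to the filter is inferred.** Adherence is also described through use of the home app and tracker recording time. Counting 21 of 26 sessions is one reading of the rule. The CG had no weekly sessions, so the session shortfall concerns the EG only.
4. **Efficacy is exploratory and unpowered.** Mixed follow-up cannot overturn a confirmatory claim. This does not cover retention and adherence, which are feasibility outcomes. Detailed handling of unequal intervals is commonly left to an analysis plan, and its absence from the article is not the finding. The finding is the incompatible statements.

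**Conclusion.** The sentence saying that April still left time for 80% of the trial is wrong on the article's own dates and design. With the latest possible end, an April entrant had 50% to 66% of 6 months, or 14 to 18 of about 26 sessions. Nobody who started after 31 January 2024 could have a 6-month T2 or meet the retention definition, and nobody who started after about 7 to 13 March could reach 80% of the planned course. This rests on a 31 July end, on a start at recruitment, and, for the session counts only, on the derived total of 26.

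A reader might go further and infer that the trial's retention, adherence and 6-month results are wrong. The article does not support that. It gives neither the number and arm of late entrants nor the adherence denominator, so the size and even the presence of a material bias cannot be computed. What is shown is that, for any such entrants, retention as defined fails by calendar, the 80% rule is ambiguous, and the 6-month label on T2 cannot be right if T2 was held within the stated dates.

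**What to change.** - Correct the 80% sentence in Results to the exposure that was possible by start date, and reconcile it with the weekly 6-month course, T2, the retention definition and the 80% adherence rule.
- State the adherence denominator: planned sessions, or sessions available to that participant.
- Report retention among participants whose start date allowed 6 months before their site closed, and list calendar-truncated participants separately.
- Report the actual T0-T2 interval by arm, with a sensitivity analysis restricted to true 6-month T2 visits.

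The cost is a text correction and some recomputation, assuming that entry, session and visit dates are on file. The retention denominator becomes smaller, and so does the sample in the restricted analysis, which matters with 9 controls. The article says that analysis is complete but results are still to be published, so the changes can go into the results report.

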### Study Design

The PoC was structured as a controlled longitudinal pilot study, with a before-and-after design, where observations were run on a series of enrolled individuals, who received the intervention described later, with data collected before and after the installation and use of the technical solution. The goal of trial evaluation was to demonstrate the viability of engAGE technology integration into everyday life to counteract cognitive decline. As secondary outcomes, the impact on the social dimension and quality of life of end users was evaluated. Moreover, acceptance over 6 months and the usability of proposed solutions were evaluated to understand the feasibility of the intervention. Despite the choice to structure the PoC as an RCT in order to provide more robust evidence on feasibility and efficacy [22,23], a formal sample size calculation was not performed. Practical constraints within the project were considered while deciding the number of end users to enroll. In fact, recruitment timelines, availability of rooms and professionals, and technical equipment represented practical limits for the study feasibility. After considering these constraints, the sample size for the PoC was set to 80 primary end users: 50 (62.5%) in the experimental group (EG) and 30 (37.5%) in the control group (CG).

In Italy, end users were recruited from the Neurology Unit and Alzheimer Assessment Unit (Memory Clinic) and from the Alzheimer daycare center of the Istituto di Ricovero e Cura a Carattere Scientifico – Istituto Nazionale di Riposo e Cura per Anziani (IRCCS INRCA). The research team could communicate with potential participants of previous projects and initiatives, as well as with other people who might have been be interested in contributing to the project evaluations. This method made it possible to be in contact with clients met before and with whom a relationship of trust was already established.

In Norway, participants were recruited from two daycare and housing centers in the city of Arendal. The first one, Solhaug, is a daycare center for old residents living in their own homes, while the second one, Plankemyra, is a combined housing and daycare center.

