### Recruitment

A specific number of people were recruited for the study via health care institutions or health care organizations. Potential participants were evaluated by eligible professionals through face-to-face interviews to verify that eligibility criteria were met. Those who did not meet the criteria or declined participation were excluded. The remaining participants were randomly assigned to the EG or the CG. A randomization technique, conducted by a statistician, based on a single sequence of random assignments was adopted. A list of random numbers was generated by the computer, while subjects were assigned a number based on their order of inclusion in the study. According to this technique, in Italy and Switzerland, the 30 subjects were randomly assigned to one of the two study groups (n=20, 66.7%, in the EG and n=10, 33.3%, in the CG), while in Norway, 20 subjects were equally assigned to the two groups. Next, for both groups, we took careful note of who were lost to follow-up, who discontinued intervention, or who were excluded from analysis. The procedure adopted is summarized in Figure 3.

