### Limitations

Although the engAGE project aims to represent an important step toward developing integrated digital health solutions for older adults with MCI, several limitations should be acknowledged. Despite the study being structured as an RCT, the sample size was not computed, and the number of end users enrolled was relatively small (N=80), limiting the generalizability of findings to larger populations. Due to the focus on the feasibility and initial efficacy of the intervention, the findings should be used to inform future sample size calculations and refine intervention protocols for future studies that aim to demonstrate the efficacy of the engAGE platform. Participants were recruited from health care organizations and daycare centers located in city areas, introducing a potential bias: people with less access to health and digital services were not considered. However, to make results more generalizable, the study was conducted across three European countries (Italy, Norway, and Switzerland) that show differences in cultural and health care contexts.

The duration of the study (ie, 6 months) was minimal, as it was unlikely to observe significant changes in cognitive capacity or the caregiver burden. Moreover, ML algorithms are designed to personalize interventions based on user data, and the study duration could not be sufficient to fully profile individual preferences or needs, making the personalization inefficient. Finally, the complexity of the platform due to the integration of several technologies, services, and ML algorithms introduced ethical concerns and exposed the users to risks in terms of data protection. However, both data protection and ethical issues were considered and addressed within the engAGE project to guarantee users’ security and safety. Thus, the presented PoC should be followed by a larger structured RCT that involves a larger sample to appreciate the significant impact of the engAGE platform, including personalization functionalities, both on end users and on national health care systems.

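### The limitations give 80 as the number enrolled when 49 were, and the reported 40:9 split is very unlikely under the described randomisation and is not explained

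*Protocol article*

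**What the plan says.** Planned size and ratio (Protocol article, Study Design): "the sample size for the PoC was set to 80 primary end users", divided as "50 (62.5%) in the experimental group (EG) and 30 (37.5%) in the control group (CG").

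Method (Recruitment): "A randomization technique, conducted by a statistician, based on a single sequence of random assignments was adopted". A computer generated the list, and participants were numbered in order of inclusion. Italy and Switzerland have "n=20, 66.7%, in the EG and n=10, 33.3%, in the CG", and "in Norway, 20 subjects were equally assigned to the two groups".

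Outcome of recruitment (Results, and the same figures in the Abstract): "40 (81.6%) of the total 49 older adults with MCI were assigned to the EG and 9 (18.4%) to the CG".

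Limitations: "the number of end users enrolled was relatively small (N=80"), given as a reason why the findings generalise poorly.

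The Results section mentions difficulties in organising the trial and recruiting at the sites, but only to explain why start and end dates differed. The readable text reports no change of ratio and no departure from the list.

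**The concern.** The two statements about enrolment contradict each other. The limitation on sample size is argued from a number 63% above the true one (80/49 = 1.63), and the 9-person control arm is not mentioned there at all.

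The split is the more serious matter. No country was planned with fewer than one third controls, yet fewer than one fifth of those assigned were controls. The article calls the study an RCT, chosen to give firmer evidence on feasibility and efficacy. The Data Analysis section tests between-group differences in change scores and reports effect sizes from them, and the Limitations section offers the findings as input to later sample size calculations. If some assignments did not follow the random list, those contrasts are open to selection bias, and a caution about power does not cover that. Nine is also the most that the control arm can contribute, because the analysis is restricted to participants with at least 80% adherence.

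**Working it through.** **Inputs.** Planned 80, 50:30 (Study Design). Country plans 20:10, 20:10 and 10:10 (Recruitment). Reported 49, 40:9 (Abstract and Results). The Recruitment section speaks of 30 subjects for Italy and Switzerland; I read this as 30 in each, the only reading that sums to 80. The country split of the 49 is not given, so I show a range.

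**Reproducing the stated figures.** EG 20 + 20 + 10 = 50 and CG 10 + 10 + 10 = 30; 50/80 = 62.5% and 30/80 = 37.5%. For the outcome, 40/49 = 81.6% and 9/49 = 18.4%. All agree with the article. The planned ratio is 50/30 = 1.67:1 overall and at most 2:1 in any country; the reported ratio is 40/9 = 4.44:1.

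**Controls expected among 49.**
- All at 2:1: 49 × 1/3 = 16.3
- At 62.5:37.5: 49 × 0.375 = 18.4
- With 20 from Norway: 29/3 + 20/2 = 19.7

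**Chance of 9 or fewer controls, simple randomisation.** This is the binomial tail, the sum over k = 0 to 9 of C(49,k) p^k (1−p)^(49−k). Where Norway contributes, binomials with p = 1/2 (Norway) and p = 1/3 (elsewhere) are convolved.

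| Assumption | Probability |
|---|---|
| All 2:1, none from Norway | 0.016 |
| 5 from Norway | 0.008 |
| 12 from Norway | 0.003 |
| 20 from Norway | 0.0009 |
| 62.5:37.5 throughout | 0.003 |

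**Chance of 9 or fewer controls, fixed country lists.** The lists hold 20 EG and 10 CG places in Italy, the same in Switzerland, and 10 and 10 in Norway. The number of EG places used in each country is hypergeometric, and the three are convolved. Over every possible country split of 49 the largest value is 3.6 × 10⁻⁵ (0.0036%), at 21, 21 and 7 participants.

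**Is it only under-recruitment?** Stopping early should shorten both arms roughly in proportion. EG reached 40/50 = 80% of its target and CG 9/30 = 30%.

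**Cost in precision.** The 95% half-width for a standardised difference is about 1.96 × √(1/n₁ + 1/n₂).
- 50:30 (as planned): 1.96 × 0.231 = 0.45
- 31:18 (49 at the planned ratio): 1.96 × 0.296 = 0.58
- 40:9 (as reported): 1.96 × 0.369 = 0.72

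Under-recruitment accounts for the step from 0.45 to 0.58, and the imbalance for the further step from 0.58 to 0.72.

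**The case against.** The article is candid about its limits. It says that no formal sample size calculation was made, calls the efficacy outcomes exploratory, states that the study was not powered, and asks for a larger trial. The recruitment flowchart is not shown in the text at hand, and participant flow by country usually belongs in the results paper. This stands as far as power goes, so I do not fault the study for failing to detect an effect. It does not answer a question about how participants were allocated, nor does it remove the contradiction between 80 and 49.

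A reader might infer more than the text supports:
- That 40:9 is impossible. It is not. Under simple randomisation any split can occur, and the fixed lists hold 50 EG places. The 16 to 18 controls are an expectation, not a minimum.
- That one random sequence cannot yield exact country splits. A randomly permuted list for each country would yield them. The description is terse, not contradictory.
- That the experimental group was filled first or by availability. Nothing in the text says so.
- That the Limitations section judges precision at 80. It ties that number to generalisability only.
- That the whole loss from 0.45 to 0.72 comes from the imbalance. About half is plain under-recruitment.

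The innocent explanations are weak. Dropout does not fit, since the figures are given as enrolled and assigned, not as completers. Limits on rooms, staff and equipment bear mainly on the robot arm, whereas controls received only a booklet, and it is controls that are missing.

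**Conclusion.** The point holds in two parts. The enrolment figure in the Limitations section is a plain error: 49 were enrolled of 80 planned. The 40:9 split is very unlikely under the randomisation described, with a one-sided probability of 1.6% at most under simple randomisation and at most 0.004% if the country numbers were fixed lists. The readable text gives no reason for it. These probabilities assume 30 planned participants in each of Italy and Switzerland and cover every possible country mix. They were worked out after the split was known, so they show that an explanation is owed; they do not prove that the list was abandoned. Whether the comparison may be called randomised depends on a check that the investigators can make and the reader cannot.

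**What to change.** 1. In Limitations, replace 80 by 49 enrolled (40 EG, 9 CG) of 80 planned, and name the 9-person control arm as a limitation.
2. Check each of the 49 assignments against the statistician's list. Report allocation by country and state how 40:9 arose, including any change of ratio or departure from the list.
3. Unless adherence to the list is confirmed, describe the EG–CG comparison in Data Analysis as non-randomised, and qualify the RCT label in the title, Abstract, Goal of the Study and Study Design.

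The cost is a check of an existing list and some text edits, which can still be made before the results are published. The downside is that the trial's claim may become less favourable.
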